## Abstract

**Background:**

Infertility is defined as the inability to conceive after 12 months of unprotected intercourse. It affects approximately one in six couples seeking pregnancy in France or western countries. Many lifestyle factors of the couples’ pre and peri-conceptional environment (weight, diet, alcohol, tobacco, coffee, drugs, physical activity, stress, sleep…) have been identified as risk factors for infertility in both males and females. The high prevalence rates of unhealthy diets and lifestyles in the reproductive population of industrialized countries are worrisome. Nevertheless, adoption of a healthy lifestyle may improve fertility but lifestyle changes are difficult to achieve and to maintain due notably to behavioral factors.

**Methods:**

Consequently, we decided to propose an interventional study aimed at improving the quality of life of infertile couples before the start of assisted reproductive technology treatment. It is a randomized controlled multicentre trial. Both members of the couples are involved in an integrated global care program (PEPCI for “Parcours Environnement PériConceptionnel en Infertilité”) vs. usual care. This global intervention not only considers diet and/or physical activity but follows a holistic approach, including a multidisciplinary assessment to address complete physical, psychological and social well-being. According to patient needs, this includes interventions on weight, exercise, diet, alcohol and drugs, mental and social health.

**Discussion:**

The main objective of trial is to demonstrate that periconceptional multidisciplinary care has a positive impact on reproductive functions. We will also focus on feasibility, acceptance, compliance and conditions of success of a multifaceted lifestyle intervention.

**Trial registration:**

The trial was registered at ClinicalTrials.gov, Identifier: NCT02961907 on November 11, 2016.

## Background

### Lifestyle and infertility

Infertility is defined as the inability to conceive after 12 months of unprotected intercourse. It affects approximately one in six couples seeking pregnancy in France or other western countries [1]. Many lifestyle factors of the pre- and periconceptional environment (e.g., weight, diet, alcohol, tobacco, coffee, drugs, physical activity, stress, sleep) have been identified as risk factors for infertility in both males and females [2, 3]. Thus, the high prevalence rates of unhealthy diets and lifestyles in the reproductive population of industrialised countries are worrisome [4]. Although practitioners tend to focus more on the female environment, we believe it is also essential to consider the male environment.

#### Overweight, obesity, and metabolic syndrome

In women, it has been recognised for a long time that overweight, obesity, and metabolic syndrome have deleterious effects on fertility [5, 6]. A longer time to conceive and ovulation disorders are more often observed in overweight and obese women [7, 8]. In addition, an increased risk of miscarriages and a decrease in the chances of achieving pregnancy after assisted reproductive technology (ART) exposure have also been described [9]. A meta-analysis including 21 studies has highlighted that female obesity negatively impacts live birth rates following in vitro fertilisation with a risk ratio (RR) [(95% confidence interval (CI)] of 0.85 (0.82–0.87) [10].

Among men, existing data are more recent yet still scarce. A meta-analysis including 13,077 men concluded the deleterious impact of overweight and obesity on sperm production [11]. Obesity also appears to have a negative impact on sperm DNA integrity [12]. Furthermore, male overweight and obesity seem to be detrimental to attaining successful ART results [13, 14]. Lastly, in comparing 100 infertile couples and 100 fertile couples, we observed a link between metabolic syndrome and male idiopathic infertility [15].

#### Weight loss

Weight loss is encouraged in cases of overweight and obesity. In overweight or obese women, weight loss, even moderate, may facilitate cycle regularisation and a spontaneous recovery of ovulation [16]. Such also increases spontaneous pregnancies [17, 18]. Nevertheless, the impact of weight loss on the chances of success in ART is less obvious [19, 20]. Mutsaerts et al. recently reported that rates of ongoing pregnancy and clinical pregnancy were not different between obese infertile women who have followed an interventional program aiming to achieve weight loss and those receiving prompt infertility treatment [19]. The authors suggested that a more intensive program or one involving better strategies to enhance adherence might have resulted in a better rate of pregnancy.

Concerning trials focused on the reproductive functions of obese men, an improvement in hormonal balance and erectile function has been observed after weight loss [21]. However, the impact of weight loss on sperm parameters or on ART results has rarely been studied. Only two studies including 43 and 200 men, respectively, have observed an improvement in sperm parameters after weight loss [22, 23]. Elsewhere, one study highlighted an improvement in sperm DNA integrity after weight loss in 126 obese men [24].

#### Physical activity

Although limited, some observational studies have highlighted the importance of moderate physical activity for fertility in both males and females [25, 26]. Recently, in a case–control study involving 302 men and women, we observed that physical inactivity was correlated with infertility in men [odds ratio (OR): 2.20; 95% CI: 1.06–4.58]. In this study, sedentary behaviour was also linked to female infertility (OR: 3.61; 95% CI: 1.58–8.24) [27].

#### Diet quality pattern

Overweight and obesity are not the only factors to consider; adequate diet and an appropriate intake of recommended daily allowances are similarly crucial to the success of pregnancy [28, 29]. Indeed, several studies have shown the deleterious effect of certain eating behaviours on male and female reproductive functions; for example, an insufficient intake of vegetables and fruits, cereals with sufficient fibre, foods rich in omega 3 (e.g., fatty fish, avocados), poultry, foods rich in antioxidants, and low-fat dairy products increases the risk of infertility. In addition, high rates of consumption of high-fat dairy products (cheese), potatoes, soy-based foods, red or processed meat, saturated fatty acids and sugars, coffee, and alcohol are harmful [30–32].

#### Other lifestyle factors

Besides diet and physical activity, addiction (tobacco, alcohol, and drug use), stress, and sleep are other modifiable factors that should be considered. It is recognised that a high level of consumption of tobacco, alcohol, or caffeinated beverages can have a negative impact on both female and male fertility [3, 33–35]. Stress has been associated with a negative impact on male fertility (i.e., on sperm concentration, mobility, and morphology) [36]. In females, stress may increase the time to pregnancy (TTP) [37] or accelerate ovarian reserve exhaustion in young women [38]. Sleep disturbances have been associated with altered semen parameters [39]. In women, it was suggested that sleep disturbances (and inherent circadian rhythm) lead to menstrual irregularities [40] and are associated with reproductive dysfunction [41].

### Adoption of a healthy lifestyle and fertility

Consequently, adoption of a healthy lifestyle may improve fertility as observed by several research teams [16, 42–44] including ours [45]. However, lifestyle changes are difficult to achieve and to maintain due notably to behavioural factors.

A Cochrane review indicated that no randomised controlled trial had yet assessed the effects of preconception advice or interventions on the chance of a live birth or other fertility outcomes in humans. The authors highlighted the need for further research in this important field [46].

Furthermore, despite the available knowledge on the relationship between poor nutrition or unhealthy lifestyle and the risk of infertility, congenital malformations, and maternal complications, health professionals and parents-to-be often remain unaware of the adverse effects of such a lifestyle [47].

Another key point is the target: most, if not all trials, focus on women only, although (1), unhealthy behaviours negatively affect the reproductive function of both parents; (2) a child is a common project; and (3) emulation can help parents to support each other, while the inclusion of both parents, even the one without any obvious lifestyle problems, might be viewed as a less confronting and more acceptable approach [48, 49].

Lastly, because interventions cannot fit all populations in the same way, tailoring intervention content and offering personalised behavioural and action feedback might increase the effectiveness of the programs compared to generic or so-called ‘one-size-fits-all’ interventions [50]. However, busy work schedules and travel constraints may affect participation rates, so, relative to face-to-face interventions, video-conference counselling sessions delivered via the Internet are more easily accessible and cost-effective. Online communication favours the multiplication of assessment points over time that allow for dynamically tailored interventions, which are credited to be more effective [51]. Thus, ease of use and high personal relevance for participants may also limit dropouts during the study [52]. Indeed, previous studies on computer-tailored web-based interventions reported positive results for a variety of health behaviours [53].

The available evidence justifies a reorganisation of infertility care for those who intend to change their unhealthy lifestyles, which includes a global preconceptional evaluation and personalised face-to-face counselling [43, 54]. Thus, we have decided to propose an interventional study aimed at improving the quality of life of infertile couples before the start of ART treatment. Our global intervention not only considers diet and/or physical activity but follows a holistic approach, including a multidisciplinary assessment to address complete physical, psychological, and social well-being. According to patient needs, the intervention includes elements on weight, exercise, diet, alcohol and drugs, and mental and social health [55]. Unlike many studies that included only overweight or obese patients, we involve both members of the parents-to-be with a body mass index (BMI) of less than 49 kg/m^2^.

## Objectives and outcomes

The main objective of this randomised study is to demonstrate that periconceptional multidisciplinary care aiming to evaluate and optimise habits of infertile couples (i.e., diet and lifestyle factors) has a positive impact on reproductive functions as a whole, including birth issues, relative to a routine approach. We will also focus on feasibility, acceptance, compliance, and conditions of success of a multifaceted lifestyle intervention.

The primary outcome of this trial is the rate of clinical ongoing pregnancies (ultrasound determination of a gestational sac at 6 weeks of amenorrhea), either after the first ART attempt performed within three to 12 months of the initial visit or during a spontaneous pregnancy occurring within 12 months after the initial visit. Couples who do not conceive during the study period (within 12 months of the initial visit) will be considered as failures. Ultrasound performed at 6 weeks of amenorrhea will be performed by an operator blinded to the intervention arm.

The secondary outcomes will allow us to compare the two arms of the trial regarding (1) the couple’s adherence, satisfaction with the program, and understanding of the importance of receiving care; (2) changes in risk factors (e.g., nutrition, addiction, physical activity, psychological factors); (3) evolution of metabolic biomarkers (including folic acid); (5) sperm quality evolution (conventional semen parameters and DNA integrity); (5) TTP; and (6) quality of life. In cases of ART, we will assess outcomes including fertilisation rate, top quality embryo rate, implantation rate, and the number of ART procedure attempts needed to achieve pregnancy within 12 months.

The tertiary outcomes concern a subgroup of pregnant women followed until delivery, through evaluation of (1) maternal complications and pregnancy outcomes (e.g., prematurity, pregnancy living), (2) newborn check-up results, (3) quality of breast milk, and (4) further analyses of collected cord blood.

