### Sample size and statistical analysis

We have considered (1) that the PEPCI intervention would lead to a relative risk of clinical pregnancy of 1.6 [28] as compared with usual care (i.e., from 20 to 32% in absolute values, respectively) and (2) that refusal of PEPCI experimental care would intervene for 20% of subjects. The resulting difference, according to the intention-to-treat principle, would therefore be 20% versus 29.6%. Given a two-sided alpha error of 5%, a power of 80%, and a randomisation ratio of 2:1 (control group:experimental group), 466 couples receiving usual care (control group) and 233 couples in the experimental group are required. The total sample size was set to 750 couples (500 control group and 250 experimental group participants), allowing room for a 5% dropout rate.

A flowchart will be used to depict the total participants of each cohort, those per group, and those per gender. All eligible participants will be included in the analyses (since they belong to the global observational cohort), and groups—that is, the randomised control group versus experimental group, encompassing couples having accepted PEPCI and couples having refused PEPCI—will be compared according to the intention-to-treat principle. General and baseline characteristics will be compared between the groups.

An analysis of the primary objective (i.e., the effect of intervention on clinical pregnancy) will be performed with a logistic regression mixed model, with a fixed factor corresponding to the randomisation-arm intervention group and the centre being considered as a random factor. The intervention group will be considered as superior if the lower-limit 95% CI of the corresponding OR of pregnancy is greater than 1. In addition, as a non-negligible proportion of couples may refuse to receive the intervention being trialled, the intention-to-treat analysis may, therefore, dilute any treatment effects. Thus, we will use the statistical method complier average causal-effect analysis, which provides unbiased estimates of the treatment effect for patients who comply with the protocol. This will be considered as a secondary analysis.

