The analysis of the effect of the intervention on other criteria (e.g., adherence, satisfaction, BMI and diet, physical activity level, quality of oocytes and semen, fertilisation rate, pregnancy, occurrence of complications) will be performed by a generalised linear mixed-regression model; its link function and distribution of errors will be chosen according to the nature of the response.

No interim analysis will be performed.

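### The ART secondary outcomes are compared between arms only in couples who reach ART, and attempts to pregnancy only in those who conceive, so these comparisons do not keep the randomised groups

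*Protocol article*

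**What the plan says.** In the protocol article, Objectives and outcomes introduces the secondary outcomes with the words "The secondary outcomes will allow us to compare the two arms of the trial". The same paragraph then narrows the population for one group of them: "In cases of ART, we will assess outcomes including fertilisation rate, top quality embryo rate, implantation rate". It closes with "the number of ART procedure attempts needed to achieve pregnancy within 12 months".

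Sample size and statistical analysis states that the intervention's effect on the other criteria, with fertilisation rate among the examples, "will be performed by a generalised linear mixed-regression model". That section also says that all eligible participants are analysed by intention to treat. Nothing in the article labels the ART outcomes as descriptive or discusses selection into ART.

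Three further statements bear on the point:
- ART interventions places the first ART attempt between 3 and 12 months after M0. The three-month programme therefore comes first. A staff meeting chooses the strategy, which may be ovarian stimulation, IUI or IVF/ICSI.
- The primary outcome counts a spontaneous pregnancy within 12 months as a success and couples who do not conceive as failures.
- Time to pregnancy is a separate secondary outcome and is not restricted to ART.

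**The concern.** Randomisation makes the arms comparable at M0. It does not make the couples who later reach ART comparable, because a couple that conceives first never enters that set. The programme is meant to affect conception, and the Background section on weight loss says that weight loss in overweight or obese women increases spontaneous pregnancies. If the programme does this unevenly across prognosis, the ART subsets differ in prognosis by arm even when nothing about ART itself has changed. Fertilisation and embryo rates narrow the set again, since couples treated only by IUI have neither.

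The attempts outcome goes one step further. A number of attempts needed to achieve pregnancy does not exist for a couple without a pregnancy, so as worded it conditions on the event that the trial is testing. A programme that helps harder cases conceive on a second or third attempt adds high counts to its own arm.

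At stake is the reading of the secondary results: a regression coefficient for arm in these subsets would be presented as an intervention effect when it is not a randomised comparison.

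**Working it through.** **The plan's own figure.** The design assumes "a relative risk of clinical pregnancy of 1.6" (20% to 32%) and that "refusal of PEPCI experimental care would intervene for 20% of subjects". The diluted experimental rate is 0.8 × 0.32 + 0.2 × 0.20 = 0.296. Use the pooled-variance formula with control rate p₁ = 0.20, experimental rate p₂ = 0.296, and r = 0.5 experimental couples per control:

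- p̄ = (2 × 0.20 + 0.296)/3 = 0.232
- n(control) = [1.960 × √(0.232 × 0.768 × 3) + 0.8416 × √(0.16 + 0.2084/0.5)]² / 0.096² = (1.433 + 0.639)² / 0.009216 ≈ 466, with 233 experimental

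This matches the protocol. It concerns the primary outcome only and does not depend on the point raised here.

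**What the document does not give.** It gives no share reaching ART, no spontaneous pregnancy rate by arm, no success rate per attempt and no number of attempts per couple. Every rate below is assumed, to show what can happen and not what will.

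**Attempts among conceivers.** Allow up to three attempts. Assume 35% of couples have good prognosis and 65% poor, with success p per attempt. The share conceiving at attempt k is the weighted sum of (1 − p)^(k−1) × p.

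- Control (25% good, 5% poor): 12.0%, 9.65% and 7.86%, total 29.5%. Mean attempts = (12.0 + 2 × 9.65 + 3 × 7.86)/29.5 = 1.86.
- Experimental (25% and 15%): 18.5%, 14.85% and 11.97%, total 45.3%. Mean = (18.5 + 2 × 14.85 + 3 × 11.97)/45.3 = 1.86.

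A gain of 15.8 points in pregnancy leaves no trace in the mean. The result depends on where the gain falls:

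| Assumed success per attempt, control to experimental | Mean attempts among conceivers |
|---|---|
| 35:65 mix, gain in poor prognosis only (5% to 15%) | 1.86 to 1.86 |
| 35:65 mix, ratio 1.6 in both groups (25% to 40%, 5% to 8%) | 1.86 to 1.77 |
| 35:65 mix, 5 points added in both groups | 1.86 to 1.84 |
| 35:65 mix, 10 points added in both groups | 1.86 to 1.81 |
| 50:50 mix, good 30% in both arms, poor 2% to 12% (35.8% vs 48.8% conceive) | 1.79 to 1.82 |

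The measure can stay flat, fall or rise while pregnancy improves.

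**The ART subset.** Pregnancy per ART couple stands in here for the listed rates. Assume one attempt for every couple without a spontaneous pregnancy, and ART success equal in both arms within each prognosis group.

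- *Set A.* 35% good prognosis; ART success 35% (good) and 12% (poor). A share s of good-prognosis couples conceives spontaneously: 10% in control, 40% in experimental. Success in the subset = [0.35(1 − s) × 0.35 + 0.65 × 0.12] / [0.35(1 − s) + 0.65]. Control: 0.18825/0.965 = 19.5%. Experimental: 0.1515/0.86 = 17.6%. Total pregnancy is 0.035 + 0.18825 = 22.3% against 0.14 + 0.1515 = 29.2%.
- *Set B.* 50:50 mix; ART success 22% and 8%; spontaneous pregnancy 10%/2% (good/poor) in control and 34%/2% in experimental. Couples reaching ART: 94% vs 82%. Success among them: 0.1382/0.94 = 14.7% vs 0.1118/0.82 = 13.6%. Total pregnancy: 19.8% vs 29.2%, near the design rates. With a true 5% relative gain in ART success, the subset still shows 14.7% vs 14.3%.

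**Against sampling error.** In Set A about 482 control (500 × 0.965) and 215 experimental (250 × 0.86) couples reach ART. The standard error of the difference is √(0.195 × 0.805/482 + 0.176 × 0.824/215) ≈ 3.2 points. The shift of 1.9 points is about 0.6 standard errors.

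**The case against.** The strongest reply is that these rates are illustrations, and chosen ones. The flat mean of 1.86 needs a tripling of success in poor-prognosis couples with no gain elsewhere; the design's own ratio of 1.6 applied to both groups moves the mean the right way. The subset examples need a large, selective rise in spontaneous conception and still yield a shift well inside sampling error. The article does not say that the programme would take the best-prognosis couples out of ART. All of this stands, and it limits the claim to what could happen.

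A second reply is that handling of non-conceivers is ordinary analysis-plan content, that the choice of link and error distribution is left open, and that the article never states that attempts will be analysed in conceivers only. This stands in part: an unseen plan could censor non-conceivers. But the article does fix the ART restriction, the purpose of comparing arms and the wording of the attempts outcome, and it names fertilisation rate among the criteria on which an intervention effect is estimated.

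Three stronger readings are tempting and should not be drawn:
- *A programme that does nothing could look beneficial.* With no difference in spontaneous pregnancy or in success per attempt, the distortions in these examples vanish.
- *Some 70% to 80% of couples would have no attempts value.* The 20% and 29.6% rates count spontaneous pregnancies and first attempts only, whereas the attempts outcome runs over all attempts in 12 months, for which no rate is given.
- *The main result is compromised.* The primary outcome is defined in every randomised couple, with non-conceivers as failures.

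**Conclusion.** The point holds for the ART secondary outcomes. The plan as written gives arm-effect estimates in groups formed after randomisation, by an event that the programme can alter, and one outcome has no value for couples without a pregnancy. These comparisons could mask or distort an effect, on the condition that the programme changes spontaneous conception or success per attempt. The document does not allow the size or direction to be worked out; in the assumed examples the effect ranges from none to a modest reversal. The primary outcome, time to pregnancy as listed and the sample size of 466 + 233 (set at 750) are untouched. The correction is worth making because the affected results would be read as effects of the intervention.

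**What to change.** - **Replace the attempts outcome.** Use cumulative clinical pregnancy within 12 months in all randomised couples, counting spontaneous pregnancies as successes, and show it as spontaneous or by ART attempt 1, 2 or 3. This differs from the primary outcome because it includes pregnancies from later attempts. Alongside it, analyse time to pregnancy in all randomised couples with non-conceivers censored.
- **Show the selection.** Report for each arm the number and baseline profile of couples who reach ART, and of those who reach IVF/ICSI.
- **Relabel the laboratory rates.** Present fertilisation, top quality embryo and implantation rates as descriptive in the couples who reach that stage, with no claim of an intervention effect.
- **Avoid one apparent remedy.** An implantation measure per randomised couple that counts spontaneous conceivers as failures makes matters worse. In Set A, ART success per randomised couple is 18.8% vs 15.2%, an apparent harm of 3.7 points (0.18825 − 0.1515) against 1.9 in the ART subset.

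The cost is a little more analysis on data already planned, since ART interventions are collected in both arms at M12 or at pregnancy. No couples are added. The downside is that the laboratory rates lose their standing as tested comparisons between arms.

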#### Patients involved in the controlled trial (Figs. 2 and 3)

All couples recruited in this trial will be assessed at baseline (M0), while the couples who accepted to undergo the PEPCI intervention will be evaluated 3 months later (M3). Then, all couples (control and experimental arms) will be followed for 12 months (M12) or evaluated at the time of pregnancy diagnosis and then until delivery.

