#### Data collection in the case of pregnancy

The centre coordinators (a physician specialist in reproductive biology and an endocrinologist) will collect data concerning the evolution of the pregnancy until birth.

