### Perspectives

The PEPCI results might show that an early diagnosis of unhealthy habits and adherence to the recommendations of physicians and follow-up are be associated with an increased chance of ongoing pregnancy and live birth spontaneously or after the first ART treatment (IUI, IVF or ICSI).

This may also be a crucial issue considering the developmental origin of health and disease (DOHaD). Indeed, current evidence indicates that unhealthy inappropriate preconceptional diet and lifestyle in both men and women not only contributes to impaired reproduction with potential long-term consequences for parental health but also compromises the health of their offspring [82, 83].

To conclude, the proposed PEPCI project might provide evidence that programs, aimed at beneficially changing preconception nutritional and lifestyle factors, should be considered as a first-choice treatment for unexplained infertility and should be suggested to each couple before ART. This original research program could also lead to public recommendations of periconceptional habits not only for subfertile couples but for all parents-to-be.

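### Birth is part of the main objective, but no live-birth outcome is defined over all randomised couples, and the primary outcome called ongoing is a gestational sac at 6 weeks

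*Protocol article*

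**What the plan says.** Under Objectives and outcomes, the main objective is to show that the programme "has a positive impact on reproductive functions as a whole, including birth issues, relative to a routine approach". This is a comparison between arms, and birth is part of it.

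The primary outcome is "the rate of clinical ongoing pregnancies (ultrasound determination of a gestational sac at 6 weeks of amenorrhea"), after a first ART attempt made 3 to 12 months after the initial visit or from a spontaneous pregnancy within 12 months. Its denominator is clear: "Couples who do not conceive during the study period (within 12 months of the initial visit) will be considered as failures".

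No primary or secondary outcome concerns birth. Delivery appears only at the third level: "The tertiary outcomes concern a subgroup of pregnant women followed until delivery". The first item there is "maternal complications and pregnancy outcomes (e.g., prematurity, pregnancy living"); newborn check-up, breast milk and cord blood follow.

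Data collection reaches further than this outcome list. In the section on patients in the controlled trial, "all couples (control and experimental arms) will be followed for 12 months (M12) or evaluated at the time of pregnancy diagnosis and then until delivery". In case of pregnancy, the centre coordinators "will collect data concerning the evolution of the pregnancy until birth". Intention to treat over all randomised couples is stated as the general principle under Study recruitment and again under Sample size and statistical analysis. The models for other criteria name pregnancy and complications among their examples, but not live birth.

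The Perspectives say that the results might show an association with an "increased chance of ongoing pregnancy and live birth spontaneously or after the first ART treatment".

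**The concern.** The objective and the anticipated conclusion both include birth, yet no listed outcome measures birth over the couples who were randomised. The outcomes that come closest are tied to women who became pregnant. If the programme raises the pregnancy rate, the experimental arm's pregnant group includes couples who would not have conceived under usual care. Those couples may differ in age, weight or cause of infertility. A difference in prematurity, complications or births per pregnancy could then reflect who conceived and not what the programme did to the pregnancy.

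The label adds to this. A sac seen at one scan shows that a clinical pregnancy exists at 6 weeks; it does not show that the pregnancy continues. A reader who meets the word ongoing would take a positive result to be nearer to live birth than it is.

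**Working it through.** **1. The plan's own figure.** Inputs from Sample size and statistical analysis: 20% under usual care, 32% with the programme, 20% refusal, two-sided alpha 5%, power 80%, allocation 2:1.

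- Rate in the experimental arm by intention to treat: 0.8 × 0.32 + 0.2 × 0.20 = 0.296.
- Control arm size with pooled variance, no continuity correction and k = 0.5 experimental couples per control couple: n = [1.96 √(p̄q̄(1 + 1/k)) + 0.842 √(p₁q₁ + p₂q₂/k)]² / (p₂ − p₁)².
- Here p̄ = (0.20 + 0.5 × 0.296)/1.5 = 0.232 and p₂ − p₁ = 0.096. The result is 466 control and 233 experimental couples, exactly as stated.

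The calculation is right for the outcome it serves, the 6-week sac. At 500/250 its power is 82.6%.

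**2. Size of the pregnant subgroup.** At 500/250:

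- control: 500 × 0.20 = 100
- experimental: 250 × 0.296 = 74
- total: 174 of 750 couples
- net excess in the experimental arm: 250 × 0.096 = 24, and 24/74 = 32%.

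So, if the plan's assumption is true, a net 32% of the experimental pregnancies would have no counterpart among control pregnancies. Reading the 24 as individual couples who conceived only because of the programme needs the further assumption that no couple conceives only under usual care.

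**3. Live birth per randomised couple.** The article gives no rate of loss between a 6-week sac and birth. I assume a loss of 10% to 30%, equal in both arms, among pregnancies that count for the primary outcome. Each rate is multiplied by (1 − loss), so the relative risk stays at 0.296/0.20 = 1.48. The test is the one in step 1.

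| Assumed loss | Control vs experimental | Power at 500/250 | Power at 466/233 | Control arm for 80% power |
|---|---|---|---|---|
| 10% | 18.0% vs 26.6% | 77.4% | 74.6% | 535 |
| 15% | 17.0% vs 25.2% | 74.5% | 71.6% | 575 |
| 20% | 16.0% vs 23.7% | 71.4% | 68.4% | 621 |
| 25% | 15.0% vs 22.2% | 68.1% | 65.1% | 672 |
| 30% | 14.0% vs 20.7% | 64.6% | 61.7% | 731 |

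The experimental arm is half the control arm throughout. These figures do not apply to a live-birth outcome that also counts later ART attempts, because the planning rates are for the primary outcome, which admits only a first attempt or a spontaneous pregnancy.

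**4. The label.** Objectives and outcomes and the Discussion both call the primary clinical and ongoing and define it by the 6-week scan. Sample size and statistical analysis calls the same event clinical pregnancy. The Background section on weight loss, describing an earlier trial in obese infertile women, names ongoing pregnancy and clinical pregnancy as two separate rates. The article therefore merges in its own primary outcome two terms that it keeps apart elsewhere.

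**The case against.** A reader might infer that the trial has no randomised comparison of live birth at all. The article does not support that. Both arms are followed to delivery, pregnancy data are collected until birth, and intention to treat is the general rule. Counting couples without a birth as failures gives the comparison, provided that the subgroup means all pregnant women. A reader might also infer that more losses after the 6-week scan would go unseen. That is not supported either: pregnancy outcomes up to delivery are on the tertiary list, so such losses would be recorded in both arms.

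Other arguments on the plan's side also carry weight.

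- Complications, newborn findings, breast milk and cord blood can be observed only after pregnancy, and the article does not say that it will draw causal conclusions from them.
- Denominators of tertiary outcomes are often left to a full protocol or analysis plan, neither of which is shown.
- The definition of the primary stands beside its label, so what is measured is not in doubt.
- The Perspectives are hedged.
- Clinical pregnancy as primary, with birth at a lower level, is a legitimate choice.

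What remains is narrower. The article itself fixes the outcome hierarchy and the population for delivery outcomes. It puts birth into the main objective, and then names no birth outcome whose population is the randomised couples. That is a mismatch in what is stated, and it does not depend on detail that may lie elsewhere.

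**Conclusion.** The point holds as a gap in outcome definition and should be corrected. It does not invalidate the primary test or the sample size, and a live-birth comparison remains possible. As specified, the only birth-related outcomes sit in a group of about 174 women selected by the primary outcome; comparisons there are not protected by randomisation and do not by themselves support the birth part of the objective. The group size rests on the plan's own rates at full recruitment. The power of about 65% to 77% for live birth at 500/250 is illustrative: it rests on an assumed, equal loss in both arms, and unequal loss would change it. It is below 80% across that range, so live birth fits as a supportive secondary outcome and not as a co-primary. The label ongoing is a lesser fault of wording, but it affects how a positive result would be read.

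**What to change.** - Name the primary outcome clinical pregnancy (gestational sac at 6 weeks) wherever it appears.
- Add a secondary outcome: live birth per randomised couple, arising from a pregnancy that counts for the primary outcome. Couples without such a birth count as failures. Analyse it by randomised arm with the primary's mixed logistic model, and state that follow-up covers delivery of pregnancies conceived by month 12.
- State that this outcome is supportive and that the trial was not sized for it.
- State whether the tertiary subgroup is all pregnant women. Report outcomes within it as descriptive, with counts per randomised couple beside them.

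The cost is outcome wording and one more model. Follow-up to delivery is already planned in both arms, and the sample size does not change.
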